## Abstract

Essential hypertension is a polygenic cardiovascular disease that is associated with maladaptive metabolic changes. Acupuncture as a non-pharmacologic intervention is used to lower blood pressure and improve metabolic dysfunction. However, such effects have not been clinically characterized. We will conduct a randomized clinical trial to evaluate the antihypertensive effect of acupuncture among patients with essential hypertension and determine the associated metabolic improvements. This study is a phase II, two-arm, randomized, sham-controlled trial (Trial registration: ChiCTR2100043737), in which biospecimens will be collected for metabolic profiling. A total of 64 patients with a clinical diagnosis of essential hypertension will be randomly assigned to either the acupuncture or the sham acupuncture group in a 1:1 ratio. All participants will receive 10 treatments over 4 weeks, with three sessions per week for the first 2 weeks and two sessions per week for the remaining weeks. The primary outcome is the change of the systolic and diastolic blood pressure measured by the 24-h ambulatory blood pressure monitoring from baseline to 4 weeks. Secondary outcomes include the circadian rhythm of blood pressure, sleep quality measured by the Insomnia Severity Index, cognitive function measured by the Montreal Cognitive Assessment, and others. Fasting blood serum and urine samples will be collected at baseline and 4 weeks for targeted and untargeted metabolomics analysis. We will use the mixed-effects model and other related bioinformatics approaches to analyze the clinical and metabolome data. This metabolomic-based trial will provide important clinical data regarding the efficacy of acupuncture for essential hypertension to better inform evidence-based care delivery for hypertension patients. Moreover, the findings will offer important insights into the mechanism of action of acupuncture for hypertension by revealing its effect on metabolism. The results of this study will be used to inform the design of a statistically powered, multicenter, randomized trial. We will publish the study findings in peer-reviewed journals. The ethical approval of this study has been reviewed and approved by the Sichuan Regional Ethics Review Committee on Traditional Chinese Medicine (ID: 2021KL-006). The outcomes of the trial will be disseminated through peer-reviewed publications.

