Our pilot studies highlighted that the antihypertensive effect of acupuncture was associated with metabolic improvements in EH patients, possibly through modulating fatty acid metabolism and the citric acid cycle (23–25). Building on these preliminary findings, we conducted a hybrid clinical trial among patients with EH to (1) assess the efficacy and safety of acupuncture vs. sham acupuncture on the reduction of blood pressure, (2) evaluate the effect of acupuncture on EH-related sleep and cognitive symptoms and the quality of life, (3) explore potential clinical factors that are predictive of treatment response to acupuncture such as treatment expectancy, sex dimorphism, traditional Chinese medicine body constitution (TCMBC), and (4) investigate the effect of acupuncture on the targeted and untargeted metabolic profile.

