### Statistical Analysis Plan

Clinical data will be analyzed with SPSS 24.0 software (SPSS Inc, Chicago, IL, USA). Continuous variables will be presented as mean and SD or as median and interquartile if they are not normally distributed. The baseline variables will be analyzed by the independent-samples t-test and Mann–Whitney U test, where appropriate. Categorical data will be presented as percentages. We will use the mixed-effects model to compare the effect of acupuncture vs. sham acupuncture on blood pressure from baseline to 4 and 8 weeks. The fixed effects are treatment arm, time, group^*^time interaction, and baseline outcome. For metabolomics data, the multivariate and univariate analysis will be performed in combination to determine the plasma metabolites that distinguish EH patients from a healthy subjects, and metabolites that exhibit significant changes before and after treatment in each treatment arm. We will use the Partial least square discriminant analysis (PLS-DA) in SIMCA-P (version 14.0; Umetrics, Umeå, Sweden) and the MetaboAnalyst (http://www.metaboanalyst.ca/MetaboAnalyst/) to fulfill the identification of differential metabolites between groups. All statistical tests will be two-sided, and statistical significance will be set at 5%.

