## Discussions

Acupuncture reduces stress and is widely used as a non-pharmacological treatment for cardiovascular diseases and metabolic disorders (20, 47). However, the modulating effects of acupuncture on the cardiovascular and metabolic systems are not well understood so far. Here, we present the design and methodology of our ongoing randomized clinical trial which evaluates the efficacy and safety of acupuncture vs. sham acupuncture on blood pressure and metabolic profile among patients with EH. We will enroll 64 eligible patients and measure their blood pressure with the 24-h ABPM test after administrating 10 acupuncture sessions over 4 weeks. Meanwhile, we will determine the changes in the metabolic profile associated with the treatment effect, via targeted and untargeted metabolic profiling. Additionally, we will identify potential clinical variables and metabolic signatures that are predictive of treatment response to acupuncture among patients with EH. The study findings may have important clinical and research implications.

Till now, the role of acupuncture in blood pressure management remains unclear. Our previous systematic review of randomized clinical trials found inconsistent results concerning the effect of true vs. sham acupuncture on blood pressure, due to the risk of bias associated with sample size, control arms, and treatment population (16, 20, 48). Further, our understanding of the biological foundation of acupuncture is limited, especially in terms of cardiovascular and metabolic modulation. Although metabolic dysregulation has been closely linked to the pathogenesis of EH (49–51), fewer studies have been conducted to assess the metabolic changes in the non-pharmacological blood pressure treatment (23). Our study incorporates metabolomics technology in the design of a rigorous randomized control trial to characterize the metabolic signatures associated with changes in clinical outcomes. This study will provide preliminary data to support the design of a sufficiently powered, randomized controlled trial in the future, which will provide important clinical data to inform the non-pharmacologic management of EH, and physiological information to understand the biological underpinnings of acupuncture for blood pressure and metabolism regulations.

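### The metabolomic analyses stated (patients versus healthy subjects, and before versus after within each arm) do not support conclusions about metabolic improvement or mechanism due to acupuncture

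*Protocol article*

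**What the plan says.** The purpose in the Abstract is to "evaluate the antihypertensive effect of acupuncture among patients with essential hypertension and determine the associated metabolic improvements". It adds that "the findings will offer important insights into the mechanism of action of acupuncture for hypertension by revealing its effect on metabolism". The Discussions section says "we will determine the changes in the metabolic profile associated with the treatment effect", and also speaks of metabolic signatures tied to clinical outcomes and to treatment response. The numbered aim in the Introduction is narrower: to "investigate the effect of acupuncture on the targeted and untargeted metabolic profile".

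The Statistical Analysis Plan section then says what the metabolomic analysis will determine:

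- It will "determine the plasma metabolites that distinguish EH patients from a healthy subjects".
- It will find "metabolites that exhibit significant changes before and after treatment in each treatment arm".
- PLS-DA is to be used "to fulfill the identification of differential metabolites between groups". The groups are not defined.

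The only regression model in that section concerns blood pressure: "We will use the mixed-effects model to compare the effect of acupuncture vs. sham acupuncture on blood pressure from baseline to 4 and 8 weeks". Its fixed effects are arm, time, their interaction and the baseline outcome. The Abstract mentions the mixed model and other bioinformatics approaches for clinical and metabolome data together, without saying which question each one answers.

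**The concern.** The announced conclusions have three parts: the metabolic change is due to acupuncture, it is an improvement, and it goes with the fall in blood pressure. Each part needs its own comparison.

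- **Due to acupuncture.** This needs the randomized contrast with sham. Testing before against after in each arm discards that contrast. Both arms receive the same lifestyle education on diet, weight and exercise (Acupuncture Intervention; Sham Acupuncture Intervention), which could itself move metabolites in both arms.
- **An improvement.** This needs a stated criterion for movement toward healthy levels.
- **Linked to the antihypertensive effect.** This needs metabolite and pressure in the same analysis.

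If the plan is followed as written, a metabolite that shifts equally in both arms can enter the acupuncture list by passing the 5% threshold there and missing it under sham. It could then be reported as part of how acupuncture works. The trial's comparison of blood pressure is not affected.

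**Working it through.** No figure in the plan bears on this point, so there is none to reproduce. The check sets each claim against the stated analyses and then sizes two consequences.

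**1. Claims against analyses**

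| Claim | Comparison needed | Stated in the Statistical Analysis Plan section? |
|---|---|---|
| Acupuncture changes the profile (aim 4) | Acupuncture versus sham, on metabolite change | Not clearly: before/after within each arm; PLS-DA groups undefined |
| The change is an improvement | Direction relative to healthy level, with a rule | Two separate contrasts; no rule joining them |
| The change goes with the blood-pressure effect | Metabolite and pressure in one model | No; the mixed model is for blood pressure only |

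**2. What within-arm testing does when the arms do not differ**

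Inputs from the Sample Size section: 32 per arm and 20% dropout, so 32 × 0.8 = 25.6, about 26 completers per arm. The test level, from the Statistical Analysis Plan section, is 5% two-sided. Assumed: pre/post correlation ρ = 0.6, unit SD, and the same shift of 0.4 SD in both arms.

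- SD of the within-patient change = √(2(1 − ρ)) = √0.8 = 0.894.
- Noncentrality of the paired t-test = 0.4 × √26 / 0.894 = 2.28.
- Probability p of significance in one arm (noncentral t, 25 df) = 0.59.
- Probability of significance with acupuncture and not with sham = p(1 − p) = 0.59 × 0.41 = 0.24.
- A direct between-arm test of change is significant with probability about 0.05, since the arms do not differ.

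A simulation under the same assumptions gave 24.4% and 4.9%. With no shift in either arm, the same pattern occurs at about 0.05 × 0.95 = 4.8%, so the excess comes from the shared shift.

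Range: for a shared shift of 0.4 SD and ρ from 0.3 to 0.7, p runs from 0.38 to 0.72 and p(1 − p) from 0.20 to 0.25. With larger shared shifts p(1 − p) falls because both arms become significant. The acupuncture list then holds even more metabolites that moved equally under sham.

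**3. Whether a blood-pressure link can be estimated from the data planned**

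Table 1 of the article puts serum and urine metabolites and 24-h ABPM at weeks 0 and 4 in the same patients. Completers: 64 × 0.8 = 51.2, about 51. With three covariates (baseline SBP, baseline metabolite, arm), the partial correlation detectable with 80% power at two-sided 5% is

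tanh((1.96 + 0.84) / √(51 − 3 − 3)) = tanh(2.80 / 6.71) = tanh(0.418) = 0.39.

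This is for a single metabolite. With 20 targeted metabolites (an assumed number) and Bonferroni correction, 1.96 becomes 3.02, and tanh(3.86 / 6.71) is about 0.52.

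**The case against.** The strongest reply is that this is a condensed article. Its analysis section is a short summary, the Abstract allows for further bioinformatics methods, and a full protocol or analysis plan may hold the missing models. Aim 4 mentions neither normalisation nor a link to blood pressure. Metabolomics is not among the listed primary or secondary outcomes, and the trial is phase II and meant to inform a later, larger one.

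Much of this stands, and it rules out several stronger readings:

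- *That the conclusions could never be reached.* The samples, the ABPM readings and the healthy reference group would allow the needed analyses. The gap is in what is stated.
- *That a link to blood pressure is absent from the article.* The Discussions section announces it; what is lacking is a method.
- *That movement toward healthy levels cannot be seen at all.* One contrast gives the direction of abnormality and the other the direction of change, so it can be read indirectly, though without a test or rule.
- *That metabolomics is half of the trial's purpose.* Only the abstract's sentence suggests that; it is the last of four aims.
- *That the plan will be biased by overlapping the two metabolite lists.* The shared baseline values would favour apparent normalisation in such an overlap, but the plan never states that step, so an error rate for it does not measure the plan.

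The reply does not dispose of the within-arm tests. They are stated explicitly as what the analysis will determine, and they do not answer even the narrow aim 4. That is a choice fixed in the text, not detail left to another document.

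**Conclusion.** The concern holds in a limited form. The stated before/after tests within each arm cannot attribute a metabolite change to acupuncture, and the announced link to blood pressure has no stated analysis. The improvement and mechanism conclusions therefore do not follow from the analyses stated.

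The misattribution rate of about 24%, against about 5% for a direct comparison, is an illustration. It rests on an assumed shared shift of 0.4 SD, an assumed pre/post correlation of 0.6 and 26 completers per arm; the documents give no metabolite variances. The detectable partial correlation of about 0.39 applies to one metabolite before multiplicity correction. The point should be settled before the metabolomic data are analysed.

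**What to change.** In the Statistical Analysis Plan section:

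1. Make an acupuncture-versus-sham comparison of week-4 metabolites, adjusted for baseline and with multiplicity control, the basis for inference. Keep the within-arm changes as description. Define the PLS-DA groups. For metabolites that differ between patients and healthy subjects, report whether the between-arm difference is toward the healthy level.
2. For the targeted metabolites, add an exploratory model of week-4 24-h SBP on metabolite change, with baseline SBP, baseline metabolite and arm as covariates. With arm in the model this estimates covariation within arms. It complements the between-arm comparison and does not show that a metabolite carries the treatment effect.

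In the Abstract, describe these results as exploratory association and not as mechanism, because metabolites and pressure are measured at the same two time points.

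The cost is a little analysis time and a more modest claim. No new samples, visits or patients are needed.

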## Introduction

Essential hypertension (EH), or primary hypertension, characterized by sustained blood pressure elevation, is a complex polygenic cardiovascular disease associated with a high morbidity and mortality rate. Over one billion people worldwide live with EH (1). Epidemiological studies reported that the incidence of EH per year is 31.5% in the high-income countries and 28.5% in the low-income countries (2). Because of genetic predisposition and environmental exposures, EH is linked to maladaptive metabolic changes, such as impaired lipid/glucose metabolism, obesity, and vascular toxin generation (3–5). Emerging evidence suggests that metabolic change is an intermediate element of the pathogenic process for EH, which is associated with major organ damages, including cognition impairment, stroke, atherosclerosis, chronic kidney diseases, and retinopathy (6–8). Systemic treatments are critical to achieving satisfactory blood pressure control (9, 10). Antihypertensive medications are the guideline-recommended first-line treatment for hypertension. Albeit availability, antihypertensives are associated with undesirable side effects and low compliance (11, 12). Therefore, safe and proper treatments are still warranted to improve the safety and patient adherence to the conventional blood pressure management paradigm.

Lifestyle factors including food and diet, body weight, daily activity, and stress emerge as modifiers of blood pressure. Exercise and stress management that directly target lifestyle factors have been shown crucial in blood pressure management and metabolic health (12, 13). Acupuncture as a non-pharmacological intervention is used in clinical practice to treat patients with cardiovascular or metabolic disorders (14, 15). Recent clinical trials demonstrated that acupuncture significantly lowers blood pressure when compared with sham control (16–19). A systematic review study showed that acupuncture used in combination with angiotensin-converting enzyme inhibitor drugs improves the clinical outcomes of blood pressure management than drugs alone (20). Evidence from basic science studies revealed that acupuncture regulates the neuroendocrine system to lower blood pressure and exert metabolism protective effects (21, 22). Given the biological linkage between blood pressure and metabolism regulations, it remains largely unknown about the mechanism of acupuncture on blood pressure regulation and metabolism.

Our pilot studies highlighted that the antihypertensive effect of acupuncture was associated with metabolic improvements in EH patients, possibly through modulating fatty acid metabolism and the citric acid cycle (23–25). Building on these preliminary findings, we conducted a hybrid clinical trial among patients with EH to (1) assess the efficacy and safety of acupuncture vs. sham acupuncture on the reduction of blood pressure, (2) evaluate the effect of acupuncture on EH-related sleep and cognitive symptoms and the quality of life, (3) explore potential clinical factors that are predictive of treatment response to acupuncture such as treatment expectancy, sex dimorphism, traditional Chinese medicine body constitution (TCMBC), and (4) investigate the effect of acupuncture on the targeted and untargeted metabolic profile.

## Methods/Design

### Ethics Approval

The study protocol conforms to the Standard Protocol Items: Recommendations for Interventional Trials (SPIRIT) 2013 statement and standards for reporting interventions in clinical trials of acupuncture (STRICTA) (26, 27). The present study protocol has already been ethically reviewed and approved by the Sichuan Regional Ethics Review Committee on Traditional Chinese Medicine with the ethical approval number: 2021KL-006.

### Study Design

This study is a randomized controlled trial conducted at the Chengdu University of Traditional Chinese Medicine and the Geriatric Hospital of Sichuan Province, Chengdu, China. A total of 64 patients with essential hypertension and 10 healthy subjects will be recruited. 64 patients will be randomly allocated in a 1:1 ratio to either the acupuncture or sham acupuncture group. Patients will receive 10 treatments over 4 weeks. The primary outcome is the 24-h average blood pressure measured with 24-h blood pressure monitoring (24-h ABPM) at 4 weeks. Secondary outcomes include blood pressure measured at 8 weeks, the 24-h circadian rhythm of blood pressure, the sleep quality measured by the Insomnia Severity Index (ISI), cognitive function measured by the Montreal Cognitive Assessment (MoCA), TCMBC, health-related quality of life, patient's treatment expectancy, and adverse events. The details of the study design are shown in Figure 1. The timeline of recruitment, interventions, and outcome measurements is shown in Table 1.

**Figure 1 F1:**
[figure not shown]
Flowchart of the trial design.

**Table 1 T1:** Trial process chart.

**week**	**-1 week**	**0 week**	**1 week**	**4 weeks**	**8 weeks**	
	**Baseline**		**Treatment period**		**Follow-up period**	
**Enrolment**						
Eligibility test	**√**					
Informed consent	**√**					
Inclusion/Exclusion criteria	**√**					
Demographics		**√**				
Medical history		**√**				
Physical examination		**√**				
Laboratory test		**√**				
Expectation of acupuncture		**√**		**√**		
Random allocation		**√**				
**Interventions**						
Acupuncture group						
Sham acupuncture group						
**Metabolomic analysis**					
Serum metabolites		**√**		**√**		
Urine metabolites		**√**		**√**		
**Outcomes**						
24-h ABPM		**√**		**√**	**√**	
Office blood pressure			**√**	**√**		
TCMBC		**√**		**√**	**√**	
ISI		**√**		**√**	**√**	
MoCA		**√**		**√**	**√**	
SF-12		**√**		**√**	**√**	
**Participants' safety**						
Adverse event						
Safety assessment						
Causes of dropout				**√**	**√**	
Compliance analysis				**√**	**√**	

### Participants

#### Recruitment Strategies

We will enroll participants from the Chengdu University of Traditional Chinese Medicine, the Geriatric Hospital of Sichuan Province, and their local communities. We will use different recruitment strategies such as posters, leaflets, social media, and free medical consultations to inform and recruit potential patients. We will also enroll patients from physician referral.

#### Eligibility Criteria

##### Hypertension Patients

###### Diagnostic Criteria.

The patient will be diagnosed with essential hypertension according to the 2017 ACC/AHA Clinical Practice Guidelines (16).

###### Inclusion Criteria.

(1) Between 18 to 60 years old, (2) free from any kind of drugs at least 2 weeks before inclusion, (3) naivety to acupuncture treatment for hypertension, and (4) willingness to participate in this study and provide written conformed consents.

###### Exclusion Criteria.

(1) With serious primary diseases such as cardiovascular, cerebrovascular, kidney and hematopoietic system, or metabolic diseases such as diabetes and thyroid dysfunction; (2) with skin diseases and skin damage on the skin or acupoints of the test site; (3) women with pregnancy or lactation or have pregnancy plans in the past year; (4) with history of epilepsy and obstructive sleep apnea syndrome; (5) with history of severe mental disorders or psychoactive substance dependence; (6) with abnormality in a laboratory test of blood biochemistry or with contagious risks; (7) used to suffer from acute diseases in recent 2 weeks, such as high gastritis or fever; (8) once received acupuncture treatment; (9) participating in other clinical trials.

##### Healthy Subjects

Healthy subjects of similar age, body mass index (BMI), and gender will be recruited mainly from the local communities. These participants have no functional or organic disorders, are not suffering from the common cold or other conditions, and have not received acupuncture treatments or taken medications within the past three months. In addition, alcoholics, smokers, and women with pregnancy or lactation will not be included.

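### Healthy controls are screened for smoking and three months of medication but patients are not, so the patient-versus-healthy metabolite comparison is open to confounding by design

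*Protocol article*

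**What the plan says.** Under Healthy Subjects, the protocol article sets the rules for the 10 controls. They are chosen to resemble the patients on three factors: "Healthy subjects of similar age, body mass index (BMI), and gender will be recruited mainly from the local communities". They are then filtered further. They must "have not received acupuncture treatments or taken medications within the past three months", and "In addition, alcoholics, smokers, and women with pregnancy or lactation will not be included".

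The patient rules are looser on two of these points. Under Inclusion Criteria, patients must be "free from any kind of drugs at least 2 weeks before inclusion". Under Exclusion Criteria, nine items are listed and none names smoking. The nearest excludes people "with history of severe mental disorders or psychoactive substance dependence".

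Under Statistical Analysis Plan, one stated aim of the metabolomics work is to find the "plasma metabolites that distinguish EH patients from a healthy subjects", by multivariate and univariate methods together. The discriminating method is named: "We will use the Partial least square discriminant analysis (PLS-DA) in SIMCA-P" and MetaboAnalyst. No restriction or covariate is named for this comparison.

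**The concern.** A comparison of patients with healthy people is observational, so it is only as sound as the comparability of the two groups. Here the difference is written into the eligibility rules. Two exposures that can alter a metabolic profile are removed from one side and allowed on the other. Similarity on age, BMI and gender does not deal with either.

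PLS-DA looks for whatever separates the groups. It cannot tell a separation due to hypertension from one due to smoking or a recently stopped drug. A univariate test of patients against controls has the same limitation. A metabolite that responds to smoking or medication, and has nothing to do with hypertension, could therefore be reported as a marker of the disease. The bias is systematic: it does not shrink with more patients, and in an untargeted screen it can move related features together.

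**Working it through.** **Step 1. The rules side by side.**

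| Factor | Healthy controls | Patients |
|---|---|---|
| Smoking | Excluded | No criterion; substance dependence excluded |
| Medication-free period | Three months | At least two weeks |
| Alcohol | Alcoholics excluded | Substance dependence excluded |
| Age, BMI, gender | Chosen to be similar to patients | Reference group |

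The Sample Collection and Preservation section sets limits before sampling on alcohol, coffee and supplements (48 h), strenuous exercise (24 h) and food (12 h). It does not list tobacco. The smoking and medication rows differ. The alcohol row is close to equal: the substance-dependence exclusion plausibly covers alcohol dependence, and the 48-h limit adds to it. Alcohol is therefore not part of this point.

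**Step 2. Size of the bias.** The plan gives no figure to reproduce. From the document: 64 patients, 10 controls, two-sided 5% tests. Assumed, because the documents do not give them: a share *p* of patients smoke; smoking shifts a metabolite by *s* SD, the SD being that within smokers or within non-smokers; hypertension has no effect on it. No control smokes. The expected patient-minus-control difference is then

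bias = *p* × *s*.

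The standard error of the difference, in units of that SD, is about

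SE = √(1/64 + 1/10) = √0.1156 = 0.34 SD.

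This ignores one detail. Mixing smokers and non-smokers raises the variance among patients to 1 + *s*² *p*(1 − *p*), for example 1 + 1 × 0.5 × 0.5 = 1.25 at *p* = 0.5 and *s* = 1. A plain normal approximation with SE 0.34 would therefore overstate the rejection rates: it gives 9%, 14% and 31% for *p* = 0.2, 0.3 and 0.5 at *s* = 1.

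**Step 3. Rejection rates by simulation.** Draw 64 patients, each a smoker with probability *p*, and 10 non-smoking controls; add *s* to smokers; apply the pooled t-test at 5%.

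| *p* (assumed) | Bias, *s* = 1 | Rejects | Bias, *s* = 0.5 | Rejects |
|---|---|---|---|---|
| 10% | 0.10 SD | about 5% | 0.05 SD | about 5% |
| 20% | 0.20 SD | about 7% | 0.10 SD | about 6% |
| 30% | 0.30 SD | about 11% | 0.15 SD | about 7% |
| 50% | 0.50 SD | about 24% | 0.25 SD | about 10% |

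With the Welch test at *s* = 1, the rates for 20/30/50% are about 9%, 13% and 27%. The nominal rate is 5%, so the effect runs from negligible to roughly a fivefold rise. It applies only to metabolites that respond to smoking.

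**Step 4. The medication difference.** The same formula applies, with *p* the share of patients who took a drug between two weeks and three months before entry and *s* its residual effect on the metabolite. The documents give neither, so no separate figure is offered. Some such patients are to be expected: the Introduction describes antihypertensive drugs as the guideline-recommended first-line treatment, and the inclusion rule admits a patient two weeks after stopping. But two weeks is a minimum, and never-treated patients also satisfy it.

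**Step 5. Precision if the patient group is restricted.** SE = √(1/*n* + 1/10):

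- all 64 patients: 0.34 SD
- 35 patients (assumed): √(0.0286 + 0.1) = 0.36 SD
- 10 patients (assumed): √(0.1 + 0.1) = 0.45 SD

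**The case against.** Four arguments weigh against the point.

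- **Ancillary role.** None of the four aims in the Introduction is a comparison with healthy subjects, and 10 controls suggest an exploratory purpose. This stands and sets the weight of the point.
- **Condensed article.** Covariates and subsets for an exploratory analysis often sit in a fuller plan that is not shown, and medical history is already taken at week 0, possibly including smoking. This stands in part: the absence of a named adjustment is not itself the fault. The unequal eligibility rules are, and they are stated in full.
- **Unknown size.** Nobody can say from the document how many patients smoke or recently stopped a drug. The substance-dependence exclusion might remove some nicotine-dependent patients, and the exclusions for diabetes, thyroid dysfunction and abnormal biochemistry narrow other metabolic differences. This stands. A reader might infer that the disease signature is confounded and that smoking metabolites will appear in it. The text supports only that the comparison is open to this.
- **Limited consequences.** A reader might also infer that this list decides which metabolites count as hypertension-related in the rest of the trial. The document does not say so. The Statistical Analysis Plan section sets the patient-versus-healthy comparison and the before-after changes in each arm next to each other, without making the first a filter for the second. The targeted panel comes from the Krebs cycle and earlier studies (Metabolomics Analysis section).

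**Conclusion.** The point holds in a limited form. The eligibility rules let smoking, and medication taken between two weeks and three months before entry, occur on the patient side only. A metabolite that separates patients from controls therefore cannot be attributed to hypertension on the planned comparison alone.

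Under the assumptions shown, the false-positive rate for a smoking-sensitive metabolite is about 7/11/24% at a 1-SD effect and about 6/7/10% at 0.5 SD, for 20/30/50% smokers. With 10% smokers it stays near 5%. These figures illustrate a range; they are not estimates for this trial.

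The acupuncture-versus-sham comparison and the blood pressure outcome are untouched, because randomisation is among patients only. The point is minor and concerns the interpretation of one ancillary analysis.

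**What to change.** 1. Make sure the week-0 medical history records each patient's smoking status and date of last medication. The Discussions section calls the trial ongoing, so patients already enrolled can be asked retrospectively.
2. Report the patient-versus-healthy comparison twice: in all patients, and in patients who meet the control criteria (non-smoking, no medication for three months). State how many patients are in the subset.
3. Call a metabolite hypertension-related only if the two results agree in direction and approximate size. Significance in the subset should not be the test, because the subset may be small.

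Patient eligibility and the randomised comparison stay as they are. The cost is two history items, if they are not already collected, and a few lines in the analysis plan. The downside is lower precision in the subset, by an amount that cannot be known in advance: the SE would be 0.36 SD if 35 patients qualify and 0.45 SD if only 10 do, against 0.34 SD for all 64. Because neither subset size has support in the documents, the restricted analysis should stand beside the full-sample one and not replace it.
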